## Abstract

**Background:**

Economic crises and unemployment have profound impact on mental health and well-being. Main goal of the Healthy Employment (HE) project is to enhance intersectoral actions promoting mental health among unemployed, namely through the implementation and effectiveness-evaluation of short-term and sustainable group interventions.

**Methods:**

The project follows a RE-AIM-based (Reach, Effectiveness, Adoption, Implementation and Maintenance) framework for assessing a cognitive-behavioural and psychoeducational intervention that has been developed for promoting mental health among unemployed people. It is a short-term group intervention (five sessions, four hours each, 20 unemployed persons per group) focused on mental health literacy, interpersonal communication and of emotional regulation. Implementation of the intervention will be carried out by clinical psychologists, following a standardized procedure manual. Effectiveness will be assessed through a randomized field study with two arms (intervention and control). Participants are unemployed people (18–65 years old, both genders, having at least nine years of formal education) registered at public employment centres from different geographical regions for less than 12 months (including first-job seekers). Allocation to arms of the study will follow a random match-to-case process, considering gender, age groups and educational level. Three moments of evaluation will occur: before intervention (baseline), immediately after its ending and three months later. Main outcomes are mental health literacy, mental health related personal and perceived stigma, psychological well-being, satisfaction with life and resilience. Intention-to-treat and per-protocol analyses will be conducted. Cohen’s d coefficient and odds ratio will be used for assessing the size of the intervention effect, when significant.

**Discussion:**

Scientific and clinical knowledge will be applied to promote/protect psychological well-being of unemployed people. While the first phases of the project are funded by the European Economic Area Grants, long-term assessments of the intervention require a larger timeframe. Further funding and institutional support will be sought for this purpose. Already established intersectoral collaborations are key-assets to reach long-term sustainability of this project.

**Trial registration:**

The study was registered with the Australian New Zealand Clinical Trials Registry; Prospectively registered number: ACTRN12616001432404; date of registration: 13 October 2016.

## Background

The recent European financial crisis has affected large proportions of the population in many countries, most particularly in Greece, Ireland and Portugal [1–3]. In Portugal, due to the assistance received from the European Financial Stabilization Mechanism, several harsh austerity measures were adopted, leading to budget cuts across different areas including the health sector [2]. This led to a reduced health system capacity, jeopardizing the implementation of health promoting actions and prevention programs [1, 4].

Economic crises present numerous potential challenges to mental health, such as reduced access to health care services [1, 5, 6] and deterioration of individuals’ psychological well-being as a result of job loss. Several studies have shown that in a context of recession or adverse economic climate, those affected by job loss have an increased risk of suffering from psychological disorders, including depression, anxiety, alcohol and drug abuse [5, 7, 8]. In Portugal, the unemployment rates have increased over the last 10 years. In late 2014, when the funding protocol for this project was first submitted (European Economic Area [EEA] Grants), the unemployment rate in Portugal was 13.5%. In February 2016, it was slightly lower (12.3%), but still higher than the European Community average (10.3%) [9]. Santana et al. [10] reported that the decreasing tendency of suicide rates observed between 1989 and 1993 and 1999–2003 (−5.4%) was inverted in 2008–2012 (with an increase of 22.6%).

Extensive work has been done to identify the complex links between economic downturns and suicide [11–14] or mood disorders [5, 8, 15]. For example, higher levels of rurality and material deprivation have been identified as main determinants of suicide in Portugal, in the context of the recent financial crisis [10]. Anyway, results remain conflicting. For example, it has been argued that difficult economic contexts do not necessarily imply increased adverse health (mortality rates can even fall), namely because economy slowdowns may favour healthier behaviours (e.g., as increased sleep time and physical activity, reduction of unhealthy foods and/or alcohol intake and less risky driving) [16]. Also, the relationship between unemployment and suicide is possibly moderated by available welfare-system support and expectancies of regaining meaningful employment, which are conditions that vary over time and between countries [17–19].

Professionally active-aged individuals may change between a variety of dynamic employment-related forms, ranging from unemployment or underemployment to employment or even overemployment [15, 20]. Deleterious effects of unemployment extend beyond the individual, affecting also relational, family and professional realms [21–23]. Under this last aspect, when attempting to make the transition back to paid employment, individuals can lack required or up-to-date skills, which can lead to precarious employment and increase risk of returning to unemployment [5, 7, 24–26].

The negative health effects of unemployment or underemployment can be attenuated or prevented through the implementation of wide restructuring health promotion actions [1, 27]. Psychological well-being depends upon a complex and interrelated set of individual, socioeconomic and environmental factors [28, 29]. Efficacious mental health protection and promotion actions need to involve several community domains and societal sectors (both public and private) such as primary health care services, social welfare support and promotion of active labour market programs [30, 31].

Several programs focused primarily on building capacity, resilience and enhancement of job search-related skills have been developed in different countries. Such intervention programs have revealed short and long-term positive effects in protecting psychological well-being among those unemployed [24, 32–36].

In Portugal, the weight of mental health related problems within the global burden of diseases, as well as their direct and indirect costs, are only marginally recognized [37, 38]. As a consequence, there is a clear deficit of evidence-based large-scale promotion mental health programs [39]. Indeed, in contrast to what has happened in other countries that implemented evidence-based programs to face unemployment rate increase [5, 31], only incipient and rather delayed responses have been developed to protect psychological well-being of unemployed individuals [3].

For these reasons, this community intervention project, the Healthy Employment (HE), has been developed to contribute to the protection and promotion of psychological well-being for the unemployed. The project includes policy, organizational and individual capacity-building opportunities for both the health sector and adjacent non-health sectors, by facilitating mental health impairment early-detection and intervention in individuals with signs of psychological suffering [40, 41] (Fig. 1).

**Fig. 1 Fig1:**
[figure not shown]
General conceptual framework of the HE project

Main products within the HE project context are the implementation and evaluation of a Portuguese-specific community intervention for psychological well-being promotion among unemployed individuals, promoting mental health and preventing negative health effects of economic and social adverse contexts. In order to be feasible and sustainable at long-term, the intervention was defined as low-cost and standardized. Also, the project endorses a systemic approach by enhancing socio-cognitive and mental healthcare referral skills among professionals in public employment centres.

### Aims and objectives

The main goal of this study is to implement a community-based intervention for psychological well-being protection and promotion and to assess its short-term effectiveness. Specific objectives are:(i)to implement a standardized intervention for psychological well-being promotion among Portuguese facing unemployment in two different community settings (rural versus urban settings)(ii)to assess the effectiveness of this mental health promotion intervention in terms of psychological well-being and resilience in job-searching.

## Methods/design

### Intervention description

Previous good practices (from different countries) [34, 42] and the opinion of a panel of Portuguese experts was used for the elaboration of a Portuguese cultural-specific adapted model of intervention aiming at the psychological well-being protection and promotion. More specifically, the intervention focuses on the promotion of unemployed individuals’ social, emotional and interpersonal skills. It also targets the strengthening of resilience and of the ability to overcome the adversity of unemployment, by maximizing the personal use of owns’ resources for employability enhancement and future success in re-employment. It is a short-term group intervention (around 20 h, delivered in a two- to three-weeks period) and follows a cognitive-behavioural and psychoeducational paradigm (focusing on mental health literacy). Strategic skills to be promoted are: reduction of mental health related stigma, recognition of psychological suffering (depression and anxiety), coping with depression and anxiety, effective communication and emotional regulation. Regarding the format and structure of the intervention, a maximum of five sessions, three hours each (maximum: 20 persons per group) will be followed.

The intervention was standardized (procedure manual with training and implementation material for facilitators), covering the following modules: Mental health literacy (about depression, anxiety, burnout, emotions), work-life balance, mental health related stigma (personal and perceived stigma), assertiveness training and definition of individual plans of action (defining short, medium and long term goals). Procedures of the intervention will include: roleplays, group discussion of vignettes, emotional and cognitive self-awareness, individual tasks based on cognitive-behavioural intervention (e.g., ABC task for assessing emotions, behaviours and cognitions; self-assessment assertive behaviour grill, for assessing contexts of assertiveness-related difficulties, etc.).

### Study design

The assessment of the intervention will be done according to the following RE-AIM (Reach, Effectiveness, Adoption, Implementation and Maintenance) framework [43] dimensions: reach, effectiveness, implementation and maintenance of qualities/properties.

The project’s reach assessment will be evaluated by measuring the proportion of invited users from two public employment centres that accept to participate in the intervention.

Effectiveness will be assessed through a randomized experimental field study with two arms (intervention group and control group) (Fig. 2). The intervention group will participate in the short-term cognitive-behavioural and psychoeducational sessions; the control group will receive the care-as-usual from public employment centres.

**Fig. 2 Fig2:**
[figure not shown]
Community-based randomized field: study design

The implementation assessment will be done by evaluating the extent to which the syllabus and training intervention is adequate and is accomplished across the intervention (fidelity assessment). A specific fidelity assessment form will be filled in by trainers and co-trainers (based on already existent toolkit forms) [44]. Also, trainees’ satisfaction with practical exercises will be assessed.

Finally, managers/supervisors’ willingness to replicate the intervention in other units of public employment centres will be assessed as a measure of the extent to which the intervention will be sustained over time (maintenance assessment).

### Sampling aspects

The target population of the HE intervention are unemployed people registered at public employment centres for less than 12 months (including first-job seekers). Random recruitment of participants (for both arms of the study) occurs in two employment centres (from different geographical regions), with match-to-case allocation in arms according to gender, age groups (18–24, 25–44, and 45–65 years old) and educational level (9 to 12, and more than 12 years of completed school – higher education). The full list of the two public employment centres users (with inclusion criteria) will be stratified by gender, age groups and educational level. In each combined stratum, random allocation will be done to each participant who accepts to participate.

Inclusion criteria: unemployed users from public employment centres, 18 to 65 years old, both genders, having at least nine years of formal/public education and being registered in the selected public employment centres at the moment of recruitment.

Exclusion criteria: public employment centres’ unemployed users already attending, at the moment of the recruitment, other public employment centre’s courses, or users with a diagnosed mental or physical severe or incapacitating disease or disability.

Two public employment centres/delegations from two Portuguese regions will be selected (intentional sampling) and invited to participate in the project. The involved public employment centres/delegations differ in terms of size (big dimension vs. small dimension) and type of region (rural population vs. urban population). In each centre/delegation, participants are randomly selected from the full database of users. Allocation to arms is done also in a random way, though following gender, age and educational level strata inter-arms matching.

In each of these settings, the initial (at baseline) users sample size will be of 50 participants with 50 other participants as controls. Previewing a dropout rate of 30% till the end of the project, we estimate to have a final users’ sample size of 35 participants in each of the arms, in each employment centre (70 participants per arm, in total). With this sample size, we expect to have 80% power to detect an effect size of 0,48 in mean scores of mental health literacy, psychological well-being, satisfaction with life and resilience [45].

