### Data analysis

Statistical analysis will be carried out using IBM/SPSS 21.0 (or a more updated version, at the moment of the analysis) and R packages. For all tests, the level of statistical significance will be set as α = .05.

For the effectiveness assessment, socio-demographic and outcome variables will be described for each moment of observation. Two strategies of data analysis will be done: (1) intention-to-treat (ITT), as a primary analysis, and; (2) per-protocol, as a supportive analysis. The ITT analysis (treatment as assigned approach), will consider all participants randomly allocated to each arm of the study at baseline with a last observation carried forward imputation for those who did not undergo the final evaluation. The per-protocol analysis (treatment as received approach), will include only the subset of the ITT sample who will completed the evaluations without any major protocol violations. When describing differences between intervention and control group, results from both types of analysis will be reported; for effect size assessment, only per-protocol approach results will be reported, in order to have an estimation of the impact of the treatment as received.

Univariate description of variables will be summarized by central tendency measures (means and medians, according to the normality of their distributions) and respective dispersion measures (standard deviation and range). Normality of data will be assessed through the analysis of kurtosis and skewness.

Association between nominal variables will be assessed through chi-square test (with Yates adjustment, when necessary). Continued variables will be compared (between arms, at the same momentum) by independent samples t-student test or by its non-parametric equivalent (Mann-Whitney test), when adequate.

Effect of the intervention will be studied by linear or logistic regression analysis (according to the nature of the dependent variable), having as dependent variables test-retest variations and adjusting for conceptually (and statistically) relevant variables. Model assumptions will be tested by analysis of residuals and influence diagnostics through Cook’s distance. Cohen’s d coefficient and odds ratio will be used for assessing the size of the intervention effect, when significant.

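### Allocation is described as more than one procedure and should be reduced to one random rule; the effectiveness analysis should adjust for centre and the three allocation factors as fixed covariates

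*Protocol article*

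**What the plan says.** **Allocation.** The Methods part of the Abstract says: "Allocation to arms of the study will follow a random match-to-case process, considering gender, age groups and educational level". The Sampling aspects section of the protocol article gives three descriptions:

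- "match-to-case allocation in arms according to gender, age groups" and educational level;
- "In each combined stratum, random allocation will be done to each participant who accepts to participate", after the statement that "The full list of the two public employment centres users (with inclusion criteria) will be stratified by gender, age groups and educational level";
- "Allocation to arms is done also in a random way, though following gender, age and educational level strata inter-arms matching".

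For each of the two centres the section then sets a fixed split: "the initial (at baseline) users sample size will be of 50 participants with 50 other participants as controls".

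**Analysis.** In Data analysis, continuous variables are compared between arms at each time point "by independent samples t-student test or by its non-parametric equivalent". The intervention effect is studied separately by linear or logistic regression on change, adjusting for variables judged relevant on conceptual and statistical grounds. Variables in study lists age, gender and educational level among the variables available for adjustment. It does not list centre.

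**The concern.** Read literally, the allocation descriptions call for different actions. Matching controls to cases means finding a control who fits someone already in the other arm. Allocating each accepting person at random within a stratum means that nobody's arm depends on anyone else's. Random allocation with strata matched between arms implies a restricted scheme, such as pairs or blocks. Staff following the text could carry out any of the three, and they do not give the same arms. At stake are the stated equal split per centre and the promised match on gender, age group and education.

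The analysis has a related weakness. When allocation is balanced on certain factors, the comparison should carry those factors. Otherwise the standard error includes variation that the design has already removed. Here two of the planned tests leave them out, the regression makes their inclusion conditional, and the centre within which the split is fixed is not a named covariate.

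**Working it through.** **Inputs.** From Sampling aspects: gender (2 levels), age group (3), education (2); 2 centres; 50 + 50 per centre at baseline; 30% dropout; 70 per arm at the end; 80% power for a standardised effect of 0.48. From Data analysis: alpha 0.05, with sidedness not stated.

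**Step 1. The plan's own figure.** 50 × 0.70 = 35 per arm per centre, and 35 × 2 = 70 per arm. Noncentrality = 0.48 × √(70/2) = 2.840. Two-sided power = Φ(2.840 − 1.960) = 0.811 by the normal approximation, and 0.805 by the t distribution. The smallest effect detectable at 80% is 0.477. One-sided power would be 0.884, so the stated figure is two-sided, and it reproduces.

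**Step 2. Size of the strata.** 2 × 3 × 2 = 12 per centre, and 100/12 = 8.3 people per stratum on average. Counting centre gives 24 cells. Centre is not listed as a stratifying factor, but the 50 + 50 is set within it.

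**Step 3. What each kind of rule would deliver in a centre of 100.**

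*Independent randomisation of each person:*
- P(exactly 50:50) = C(100,50)/2^100 = 0.080; in both centres, 0.006.
- 95% range for one arm: 40 to 60. Mean absolute difference between arms: about 7.9.
- Simulation (40,000 runs, equal expected strata): about 27 of 100 people have no same-stratum partner in the other arm. With an assumed uneven mix (age 15/55/30%, education 75/25%, gender even) it is about 25.
- The chance that all 12 strata are balanced to within one person is essentially zero in both cases.

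*Restricted randomisation within centre and stratum (20,000 runs, equal expected strata):*
- Pairs: mean absolute arm difference 1.9 (95% range −4 to +4).
- Blocks of 4: 2.5 (−6 to +6).
- About 6 of 12 strata hold an odd number, so even pairs leave about 6 people unmatched. The split comes close to 50:50 but is not exact.

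**Step 4. Leaving the factors out of the test when matching works.** Let R² be the share of outcome variance explained by centre and the three factors. The documents give no value, so a range is assumed. The true standard error shrinks by √(1 − R²), while the unadjusted test uses the full one:

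- true alpha = 2 × [1 − Φ(1.960/√(1 − R²))]
- unadjusted power = Φ((2.840 − 1.960)/√(1 − R²))
- adjusted power = Φ(2.840/√(1 − R²) − 1.960)

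| R² (assumed) | True alpha, unadjusted | Power, unadjusted | Power, adjusted | Gain |
|---|---|---|---|---|
| 0.05 | 0.044 | 0.817 | 0.830 | 0.013 |
| 0.10 | 0.039 | 0.823 | 0.849 | 0.026 |
| 0.20 | 0.028 | 0.837 | 0.888 | 0.051 |

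**The case against.** The best defence of the allocation text is that its parts can be read together. The Abstract calls the process random as well as match-to-case, and the last description in Sampling aspects combines randomness with matching between arms. That fits randomisation within matched pairs or small blocks, and Step 3 shows that such a scheme would bring the arms close to the stated split. An article may also leave block sizes and list generation to the full protocol. This stands. The figures for independent randomisation therefore describe one possible reading, not a procedure that the article clearly adopts. What remains is that the descriptions differ from one another and should be reconciled.

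A reader might infer that concealment is lost, because a matched partner's arm follows from the first assignment. The documents do not support that. In a randomised pair each member still has an even chance of either arm, and the second assignment is exposed only if the first is revealed before the partner is enrolled. The article says nothing of the kind. It does not mention concealment, which an article may leave to the full protocol.

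A reader might also infer that every arm comparison ignores the matching. That is not so: all three matching factors are on the list of possible regression adjusters. The gap is limited to the unadjusted tests, the conditional wording and the missing centre.

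Finally, the two problems do not add up. If allocation were unrestricted and matching failed, the unadjusted t-test would keep its nominal error rate. The conservatism in Step 4 arises only when matching works.

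**Conclusion.** The point holds at moderate size. The Abstract and Sampling aspects describe allocation in terms that are not one procedure. Of these, independent randomisation of each participant would not reliably give 50 and 50 per centre or the matching. The harm to power from unequal arms would be small: 0.805 at 70:70 against 0.797 at 60:80.

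In the analysis, the unadjusted tests leave out the allocation factors, and the regression does not guarantee their inclusion and omits centre. If matching works and the factors explain 5% to 20% of variance, true alpha is about 0.044 to 0.028, and adjustment gains about 1 to 5 percentage points of power. The present error is conservative and does not raise the false-positive risk. The R² range is an assumption. Because the regression outcome is change from baseline, the share explained by demographic factors could lie at or below the low end. The sample size calculation needs no correction.

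**What to change.** 1. In the Abstract and Sampling aspects, replace the several descriptions with one random rule and drop the match-to-case term. Suitable rules are 1:1 random permuted blocks within centre and stratum or, if strata of about 8 people are too sparse, minimisation with a random element within centre over gender, age group and education. Describe 50 + 50 per centre as the target, since either rule approximates it.
2. In Data analysis, make the adjusted regression the arm comparison for effectiveness. Include centre, gender, age group and educational level as prespecified fixed covariates whatever their significance. Keep the t and Mann-Whitney tests as descriptive.
3. In Variables in study, add centre to the adjustment variables.

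The cost is wording and a computer-generated allocation. The covariates are already known for every participant. They use 1 + 1 + 2 + 1 = 5 degrees of freedom, which takes the residual from 138 to 133 with 140 completers. No change to the sample size is needed.
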